## Abstract

**Background:**

Patients with ectopic pregnancy (EP) and low serum hCG concentrations and women with a pregnancy of unknown location (PUL) and plateauing serum hCG levels are commonly treated with systemic methotrexate (MTX). However, there is no evidence that treatment in these particular subgroups of women is necessary as many of these early EPs may resolve spontaneously. The aim of this study is whether expectant management in women with EP or PUL and with low but plateauing serum hCG concentrations is an alternative to MTX treatment in terms of treatment success, future pregnancy, health related quality of life and costs.

**Methods/Design:**

A multicentre randomised controlled trial in The Netherlands. Hemodynamically stable patients with an EP visible on transvaginal ultrasound and a plateauing serum hCG concentration < 1,500 IU/L or with a persisting PUL with plateauing serum hCG concentrations < 2,000 IU/L are eligible for the trial. Patients with a viable EP, signs of tubal rupture/abdominal bleeding, or a contra-indication for MTX will not be included. Expectant management is compared with systemic MTX in a single dose intramuscular regimen (1 mg/kg) in an outpatient setting. Serum hCG levels are monitored weekly; in case of inadequately declining, systemic MTX is installed or continued. In case of hemodynamic instability and/or signs of tubal rupture, surgery is performed. The primary outcome measure is an uneventful decline of serum hCG to an undetectable level by the initial intervention. Secondary outcomes are (re)interventions (additional systemic MTX injections and/or surgery), treatment complications, health related quality of life, financial costs, and future fertility. Analysis is performed according to the intention to treat principle. Quality of life is assessed by questionnaires before and at three time points after randomisation. Costs are expressed as direct costs with data on costs and used resources in the participating centres. Fertility is assessed by questionnaires after 6, 12, 18 and 24 months. Patients' preferences will be assessed using a discrete choice experiment.

**Discussion:**

This trial will provide guidance on the present management dilemmas in women with EPs and PULs with low and plateauing serum hCG concentrations.

**Trial registration:**

Current Controlled Trials ISRCTN 48210491

## Background

In industrialized countries the incidence of ectopic pregnancy (EP) is approximately 1 to 2% of all pregnancies [1-4]. EP is usually diagnosed by non-invasive methods, i.e. by sensitive pregnancy tests in urine and serum, and high resolution transvaginal sonography (TVS), which have been integrated in reliable diagnostic algorithms. These algorithms, in combination with increased awareness and knowledge of risk factors among both clinicians and patients, have enabled an early and accurate diagnosis of EP [5-7].

As a consequence, the clinical presentation of EP has changed from a life threatening disease, necessitating emergency surgery, to a more benign condition in frequently asymptomatic patients for whom non-surgical treatment options are available, i.e. medical treatment with systemic methotrexate (MTX) treatment or expectant management.

MTX can be administered systemically in a multiple dose regimen (MTX 1.0 mg/kg intramuscularly (im) day 0, 2, 4, 6, alternated with folinic acid 0.1 mg/kg orally day 1, 3, 5, 7) or in a single dose regimen (MTX 1.0 mg/kg or 50 mg/m^2 ^im without folinic acid) [8,9]. A single dose regimen was introduced to minimize side effects, to improve patients' compliance and to reduce overall costs. MTX has been shown to be safe with virtually no adverse effects reported on reproductive outcome [10]. Data provided by randomised controlled trials (RCTs) indicate that systemic MTX treatment should only be used in selected patients with EP. Important selection criteria are the EP size, absence of fetal cardiac activity on TVS, and maximum human chorionic gonadotrophin (hCG) concentrations [11,12].

Expectant management has been practiced based on the acknowledgement that the natural course of many early EPs is a self limiting process, ultimately resulting in tubal abortion or reabsorption. To date, expectant management has not been properly evaluated in RCTs in selected patients with EP [12].

In these non-surgical treatments, the pregnancy is not removed and as a consequence there is a remaining risk of tubal rupture. Therefore, intensive serum hCG monitoring is mandatory to detect impending treatment failure and/or inadequately declining serum hCG concentrations [13,14]. The risk of tubal rupture combined with the need for meticulous follow-up is likely to cause distress in the patient because of uncertainty about treatment outcome [15]. Non-surgical treatment modalities may therefore have a negative impact on the patients' health related quality of life.

In some women presenting with suspected EP, the pregnancy cannot be identified on TVS [16,17]. These women with a so called pregnancy of unknown location (PUL) can be managed expectantly with monitoring of serum hCG to identify whether a PUL turns out to be an intra uterine pregnancy (IUP), an EP, a failing PUL with an uneventful serum hCG decline to undetectable levels, or a persisting PUL with plateauing serum hCG concentrations [18].

Women with a visible EP but with low and plateauing serum hCG concentrations and women with a persisting PUL have thus far been offered medical treatment with MTX [17,19]. However, there is no evidence on the effectiveness of MTX as compared to expectant management. This study compares both treatment options in these particular subgroups of women, representing about 10% of women with suspected EP.

## Objective

To study whether expectant management is an alternative to treatment with systemic MTX in a single dose im regimen in women with an EP and low but plateauing serum hCG concentrations in terms of tubal rupture, future pregnancy, health related quality of life and costs.

## Methods

### Participating centres

This study is a multicentre randomised controlled trial in The Netherlands and inclusion started in April, 2007.

### Inclusion criteria

Hemodynamically stable patients ≥ 18 years of age, with either a visible EP on TVS (an ectopic ring or an ectopic mass and/or fluid in the pouch of Douglas) together with plateauing serum hCG concentrations < 1,500 IU/L, and those women with a PUL in combination with plateauing serum hCG concentrations < 2,000 IU/L, are eligible for the trial. The difference in serum hCG cut-off levels for these two entities is based on our previous studies [5,7]. Patients with a viable EP, signs of tubal rupture, active intra abdominal bleeding or a contra indication for MTX (e.g. abnormalities in liver or renal function or at full blood count) are not included.

### Ethical considerations

Approval for this study was obtained from the Medical Ethical Committee of the Academic Medical Centre and from the Central Committee on Research involving Human Subjects (CCMO), The Netherlands. A quality assessment has been made and approved by three external referees, experts from the field by the Netherlands Organization for Health Research and Development (ZonMw). A blinded interim analysis will be performed halfway the study by the Data Monitoring and Safety Committee. In patients fulfilling the inclusion criteria, written informed consent is obtained before randomisation is carried out. Women refusing participation are registered.

### Randomisation

Randomisation is performed by a web-based randomisation program, using a computer program with stratification for hospital and serum hCG concentration (< 1,000 IU/l versus 1,000–2,000 IU/l).

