#### Secondary outcome measures

Secondary outcome measures are (re)interventions (additional MTX injections or surgical procedures for persistent trophoblast and/or clinical signs), treatment complications, health related quality of life, financial costs, and future fertility. Moreover, patients' preferences will also be assessed.

Health related quality of life is assessed by standard self administered psychometric questionnaires with established viability and reliability at different time points, i.e. before randomisation, after one week, four weeks and three months.

Costs are expressed in direct costs with data on costs and used resources in the participating centres.

Future fertility is defined as time to the occurrence of a spontaneous viable IUP. A viable IUP is defined as the presence of fetal cardiac activity at a gestational age of ≥ 12 weeks. If an IUP does not occur, follow-up ends at the last consultation. In addition to IUP, repeat EP is also assessed. The date of occurrence of an EP will be determined from the first day of the last menstrual period.

Patients' preferences are assessed by an online questionnaire using a discrete choice experiment (DCE) based on characteristics of both interventions and will be compared with a control group, recruited among women visiting the infertility clinics of the participating hospitals.

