#### Power calculation

Assuming an uneventful decline of serum hCG of 60% in the expectant management group and of 90% in the MTX group, and assuming a power of 80% and a significance level of 5%, 36 patients in each group are needed [6,15,22-24].

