## Discussion

About 10% of women presenting with suspected EP, are diagnosed with a visible EP but with low and plateauing serum hCG concentrations or a persisting PUL [24]. Thus far, these particular subgroups of women are offered medical treatment with MTX based on the proven effectiveness of systemic MTX in women with selected EPs [12,16,19]. The question is whether it is really necessary to treat these women at all. This RCT will provide evidence whether expectant management is an alternative to systemic MTX in a single dose im regimen in women with an EP with low but plateauing serum hCG concentrations or persisting PUL.

Simultaneously with our trial, another trial is ongoing in the United Kingdom [20]. This placebo controlled trial has a similar objective, uses the same inclusion criteria and interventions (single shot MTX im and expectant management). In the UK trial, however, surgical intervention is installed in both treatment groups if inadequately declining serum hCG concentrations occur after one week of follow up. In our study, these treatment failures are treated with additional MTX injections. In the near future, meta analysis of the results of both trials will provide guidance on the present management dilemmas in women with EP or PUL with low and plateauing serum hCG concentrations.

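### Visible EP and PUL are pooled with no stratum and no stated analysis by diagnosis, so the trial gives a valid combined answer but only imprecise statements about each diagnosis

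*Protocol article*

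**What the plan says.** The Inclusion criteria admit women with a visible EP and plateauing hCG below 1,500 IU/L, and women with a PUL and plateauing hCG below 2,000 IU/L. They explain: "The difference in serum hCG cut-off levels for these two entities is based on our previous studies". A visible EP is defined there as "an ectopic ring or an ectopic mass and/or fluid in the pouch of Douglas". The Background, by contrast, calls a pregnancy that ultrasound cannot identify a PUL.

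The Randomisation section names its factors: "stratification for hospital and serum hCG concentration (< 1,000 IU/l versus 1,000–2,000 IU/l". Diagnosis is not among them. The Analysis section compares short-term outcomes by relative risks with 95% intervals and names no covariate or breakdown. The Power calculation uses one pair of rates for everyone, "uneventful decline of serum hCG of 60% in the expectant management group and of 90% in the MTX group", and arrives at 36 per group.

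The target population varies between sections. The Background says "This study compares both treatment options in these particular subgroups of women", meaning visible EP with low plateauing hCG and persisting PUL. The aim in the Abstract also names both. The Objective names EP alone. The Abstract's discussion says the trial will guide management of EPs and PULs, and the first paragraph of the main Discussion expects evidence on both.

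**The concern.** If the article itself regards the two diagnoses as distinct enough to need different entry limits, a reader will ask whether one pooled relative risk answers the question for each. The hCG strata do not stand in for diagnosis: both strata can hold EP and PUL, and only the range from 1,500 to 2,000 IU/L is PUL alone.

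Three things are at stake. A pooled result could be applied to a diagnosis that contributed few women. The arms could differ by chance in their mix of diagnoses. And the line between the diagnoses is unclear: a woman with fluid but no ring or mass, and hCG of 1,700 IU/L, is ineligible if fluid alone counts as a visible EP and eligible if she is classed as PUL. Any analysis by diagnosis inherits that uncertainty.

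**Working it through.** **Inputs.** From the Power calculation: 60% versus 90%, 80% power, 5% significance (two-sided assumed, since sidedness is not stated), 36 per group. The article gives no EP:PUL mix and no success rates by diagnosis, so those below are assumptions shown over a range.

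**1. The plan's own figure.** The normal approximation for 60% versus 90% gives 32 per arm without and 38 with continuity correction. Exact Fisher power at 36 per arm is 80.0%. The stated 36 is reproduced.

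**2. Precision within one diagnosis**, taking 60% versus 90% there too. The half-width is 1.96 × √((0.60×0.40 + 0.90×0.10)/n) = 1.96 × √(0.33/n).

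| Share of the trial | n per arm | Fisher power | 95% half-width, risk difference |
|---|---|---|---|
| 25% | 9 | 14% | 38 points |
| 50% | 18 | 43% | 27 points |
| 75% | 27 | 63% | 22 points |
| 100% (pooled) | 36 | 80% | 19 points |

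Eighty per cent power in each diagnosis would need 36 per arm in each, or 36 × 2 × 2 = 144 women instead of 72. Power to detect a 30-point difference in effect between diagnoses, at 18 per cell, is about 37% to 43%, depending on the assumed rates.

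**3. Dependence on case mix, if the effect differs.** Assume MTX success of 90% in both diagnoses, and expectant success of 45% in EP and 75% in PUL.

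- EP share 25%: expectant 0.25×0.45 + 0.75×0.75 = 67.5%; difference 22.5 points; relative risk 0.75.
- EP share 50%: expectant 60%; difference 30 points; relative risk 0.67.
- EP share 75%: expectant 52.5%; difference 37.5 points; relative risk 0.58.

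If the effect is the same in both diagnoses on the scale used, the pooled effect does not move with the mix.

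**4. Chance imbalance.** Treat the number of PUL women per arm as two independent Binomial(36, p) counts. The probability that the arms' PUL shares differ by 15 points or more is 19.5% at p = 0.5 and 13.3% at p = 0.25 or 0.75. This gives no credit for any balance gained through the hospital and hCG strata.

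With an assumed 30-point gap in success between diagnoses in both arms, a 15-point imbalance shifts the risk difference by 0.15 × 0.30 = 4.5 points. The smallest attainable imbalance above that mark is 6/36 = 16.7 points, a shift of 5.0. The standard error of the pooled difference is √(0.33/36) = 9.6 points, so the shift is about half a standard error (4.5/9.6 = 0.47; 5.0/9.6 = 0.52).

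The assumed gap is generous. At an even mix with 90% overall success on MTX, it would need 75% in one diagnosis and 105% in the other, which is impossible. At a 75:25 mix it is possible (97.5% and 67.5%).

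**5. Gain from adjustment** under that gap at 75:25. Diagnosis explains 0.75 × 0.25 × 0.30² = 0.016875 of the variance in each arm. The adjusted standard error is about √((0.33 − 2×0.016875)/36) = √(0.29625/36) = 9.1 points, against 9.6 unadjusted.

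**The case against.** A reader might infer that the result necessarily depends on the case mix and cannot guide either group. The documents do not support that. Randomisation makes the pooled comparison valid for the combined population, which is how the Abstract, the Background and the main Discussion frame the question. Case mix matters only if the effect differs by diagnosis, and nothing in the article says it does; separate entry limits are not evidence of it.

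Nor does the article promise a separate answer for each diagnosis. The closing line of the Discussion, that something "will provide guidance on the present management dilemmas in women with EP or PUL", has as its subject a meta-analysis with the UK trial, not these 72 women.

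Chance imbalance does not bias a randomised comparison, and the confidence interval already allows for it. With 72 women split by hospital and hCG, a third stratification factor would thin the cells further, so choosing hCG over diagnosis is defensible. Subgroup and adjusted analyses are often left to the full protocol or analysis plan, neither of which is shown; their absence from the article would not be a finding by itself.

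All of this stands and limits the point. It does not remove the stated stratification factors, which an analysis plan cannot change afterwards, the Objective that names a narrower population than the one recruited, or the conflict over fluid alone. A meta-analysis meant to inform both diagnoses would itself need results by diagnosis.

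**Conclusion.** The concern holds in a limited form. The trial pools two groups that it calls distinct entities, does not stratify by diagnosis, and states a comparison that does not mention diagnosis, while claiming guidance or evidence for both and stating its Objective for one. The combined comparison is sound and the sample size reproduces. Statements about each diagnosis would be imprecise: at an even split, about 43% power and ±27 points. That assumes the planned 60% and 90% apply within each diagnosis.

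The 22.5-to-37.5-point spread and the 4.5-point shift rest on assumed rates. They show what could happen, not what the documents establish. Missing stratification costs some balance and precision but not validity, and the gain from adjustment is small (9.6 to about 9.1 points). The change is worth making because it costs little.

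**What to change.** - Adjust the primary relative risk for recorded entry diagnosis, and for the randomisation strata where feasible. Entry diagnosis should already be on record, because it decides which hCG limit applies. Inclusion began in April 2007, so this works without altering the randomisation.
- Report success by arm within EP and within PUL, with a diagnosis-by-treatment interaction estimate. Label these exploratory and give their intervals.
- Word the main conclusion for the combined population.
- Reconcile the Objective, which names EP only, with the EP-plus-PUL population in the Abstract, Inclusion criteria and Discussion.
- Reconcile the Background and the Inclusion criteria on where a woman with fluid but no ring or mass belongs, so that the two diagnoses are mutually exclusive.

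The cost is some wording and a small amount of extra analysis, with no additional patients. The drawback is that the subgroup intervals will be wide, and a non-significant interaction must not be read as showing equal effects.

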### Interventions

Expectantly managed women will get no specific treatment.

Women in the group allocated to MTX are administered a single MTX injection, 1 mg/kg body weight im, within 24 hours after randomisation.

All Rhesus negative women will receive 375 IE anti D im. For pain relief, if necessary, Paracetamol is prescribed. Patients are advised to refrain from sexual intercourse until serum hCG is undetectable. Treatment and follow up will be carried out in the outpatient clinic (Figure 1).

**Figure 1 F1:**
[figure not shown]
Flowchart METEX study.

### Follow up

#### Short term follow up

In both groups weekly serum hCG measurements will be performed until serum hCG is no longer detectable. Serum hCG concentrations are expressed in IU/L (conversion factor to SI unit, 1.00 according to the World Health Organization Third International Standard 75/537). Seven days after a MTX injection liver and renal function and full blood count are checked. Complications will be registered in the Case Record Form.

In patients treated expectantly, treatment with systemic MTX (single shot 1 mg/kg im) is started whenever at any of the weekly follow up visits the serum hCG concentration has risen > 15% of the prior value. Expectant management is continued if the serum hCG concentration falls by > 15% of the prior value [20]. In case of a persistent plateauing serum hCG concentration, defined as < 15% fall or < 15% rise, the serum hCG concentration is assessed after 48 hours to ensure it is not increasing. If it is increasing as described above, treatment with systemic MTX as described above is installed. Whenever hemodynamic instability and/or clinical signs of tubal rupture (i.e., increasing abdominal pain in combination with falling haemoglobin level and signs of intra abdominal haemorrhage on TVS) occur, surgical intervention is carried out.

In patients treated with MTX, an additional MTX injection is given in case the serum hCG concentration on day 7 has declined <15% of the initial value on day 1 (start of treatment) [11]. If the serum hCG concentration fails to fall by at least 15% during any successive week of follow-up, repeated doses of MTX are given, with a maximum of three additional injections [21]. In case of hemodynamic instability and/or signs of tubal rupture, i.e., increasing abdominal pain in combination with falling haemoglobin level and signs of intra abdominal haemorrhage on TVS, or whenever more than four MTX injections are required, surgical treatment is indicated.

#### Long term follow up

Women who have been treated with MTX are advised not to get pregnant within three months after treatment [18]. To assess fertility in both treatment arms, patients are contacted every six months for a period of 24 months, by means of questionnaires. Questions focus on the desire for pregnancy, unprotected sexual intercourse with a chance of spontaneous conception, contraceptive use, infertility treatment, and the occurrence of any pregnancies and their outcomes.

### Outcome measures

#### Primary outcome measure

The primary outcome measure is an uneventful decline of serum hCG to an undetectable level (< 2 IU/l) by the initial intervention strategy, i.e. expectant management or a single dose systemic MTX.

#### Secondary outcome measures

Secondary outcome measures are (re)interventions (additional MTX injections or surgical procedures for persistent trophoblast and/or clinical signs), treatment complications, health related quality of life, financial costs, and future fertility. Moreover, patients' preferences will also be assessed.

Health related quality of life is assessed by standard self administered psychometric questionnaires with established viability and reliability at different time points, i.e. before randomisation, after one week, four weeks and three months.

Costs are expressed in direct costs with data on costs and used resources in the participating centres.

Future fertility is defined as time to the occurrence of a spontaneous viable IUP. A viable IUP is defined as the presence of fetal cardiac activity at a gestational age of ≥ 12 weeks. If an IUP does not occur, follow-up ends at the last consultation. In addition to IUP, repeat EP is also assessed. The date of occurrence of an EP will be determined from the first day of the last menstrual period.

Patients' preferences are assessed by an online questionnaire using a discrete choice experiment (DCE) based on characteristics of both interventions and will be compared with a control group, recruited among women visiting the infertility clinics of the participating hospitals.

